# At-home computerized executive-function training to improve cognition and mobility in normal-hearing adults and older hearing aid users: a multi-centre, single-blinded randomized controlled trial

**DOI:** 10.1186/s12883-023-03405-1

**Published:** 2023-10-20

**Keywords:** Hearing loss, Hearing aids, Aging, Falls, Dual-task, Executive function, Cognitive training, Prevention, Neuroimaging, Virtual reality

## Abstract

**Background:**

Hearing loss predicts cognitive decline and falls risk. It has been argued that degraded hearing makes listening effortful, causing competition for higher-level cognitive resources needed for secondary cognitive or motor tasks. Therefore, executive function training has the potential to improve cognitive performance, in turn improving mobility, especially when older adults with hearing loss are engaged in effortful listening. Moreover, research using mobile neuroimaging and ecologically valid measures of cognition and mobility in this population is limited. The objective of this research is to examine the effect of at-home cognitive training on dual-task performance using laboratory and simulated real-world conditions in normal-hearing adults and older hearing aid users. We hypothesize that executive function training will lead to greater improvements in cognitive-motor dual-task performance compared to a wait-list control group. We also hypothesize that executive function training will lead to the largest dual-task improvements in older hearing aid users, followed by normal-hearing older adults, and then middle-aged adults.

**Methods:**

A multi-site (Concordia University and KITE-Toronto Rehabilitation Institute, University Health Network) single-blinded randomized controlled trial will be conducted whereby participants are randomized to either 12 weeks of at-home computerized executive function training or a wait-list control. Participants will consist of normal-hearing middle-aged adults (45–60 years old) and older adults (65–80 years old), as well as older hearing aid users (65–80 years old, ≥ 6 months hearing aid experience). Separate samples will undergo the same training protocol and the same pre- and post-evaluations of cognition, hearing, and mobility across sites. The primary dual-task outcome measures will involve either static balance (KITE site) or treadmill walking (Concordia site) with a secondary auditory-cognitive task. Dual-task performance will be assessed in an immersive virtual reality environment in KITE’s StreetLab and brain activity will be measured using functional near infrared spectroscopy at Concordia’s PERFORM Centre.

**Discussion:**

This research will establish the efficacy of an at-home cognitive training program on complex auditory and motor functioning under laboratory and simulated real-world conditions. This will contribute to rehabilitation strategies in order to mitigate or prevent physical and cognitive decline in older adults with hearing loss.

**Trial registration:**

Identifier: NCT05418998. https://clinicaltrials.gov/ct2/show/NCT05418998

## Background

There is a high prevalence of hearing impairment in older adults, with up to two-thirds of adults aged 70 years and older having bilateral peripheral hearing loss [1, 2]. Epidemiological studies have demonstrated an association between hearing loss and cognitive decline [3], incident dementia [4–7], frailty and increased risk of falling [8, 9], poor balance [10], and reduced gait speed [11]. Several mechanistic theories have been proposed to explain the association between hearing loss and cognitive decline (e.g., sensory deprivation, common cause, effortful listening) [12, 13]. Effortful listening theories argue that when an auditory signal is impoverished due to hearing loss, increased attentional resources must be allocated to hearing, drawing on the same resources needed for other ongoing tasks requiring higher-level cognitive processing [12, 14, 15]. As higher level cognition is involved in the regulation of posture and gait in old age [16], competition for cognitive resources due to hearing loss can therefore lead to reduced performance on mobility tasks requiring attention.

### Empirical evidence supporting effortful listening

Substantial evidence exists in support of effortful listening theories, including studies that compare older adults with normal hearing versus older adults with hearing loss, as well as those that manipulate the level of cognitive demand or listening effort. For example, in studies where the acoustic challenge is increased (e.g., degraded speech, speech-in-noise tasks), normal-hearing individuals exhibit greater difficulty processing linguistically complex sentences, poorer speech comprehension, and reduced memory for auditory information [17]. Additionally, studies utilizing a dual-task paradigm where a cognitive load is added to a mobility task have shown that older adults with hearing loss tend to prioritize posture or walking over cognitive performance (i.e., they have greater dual-costs in the cognitive domain) [18, 19]. In concordance with effortful listening theories, this may be due to the increased attentional resources needed by older adults with hearing loss to process the auditory signal, thereby causing competition for higher level cognitive processes required during dual-tasking and promoting postural prioritization to maintain safe mobility. Finally, neuroimaging studies also lend support for this theory, with increased cortical activation found in regions implicated in cognitive control (e.g., prefrontal cortex) during effortful listening in both normal-hearing adults [20, 21] and older adults with hearing loss [22–24]. Taken together, this evidence supports effortful listening theories insofar as higher-level cognitive resources are needed to compensate for impoverished auditory inputs.

### Ecologically valid measurements of hearing, cognition, and mobility

While these findings elucidate a possible mechanism underlying the association between hearing loss and cognitive and physical decline, some researchers have argued that the typical laboratory-based approaches used to measure hearing, cognition, and mobility lack ecological validity [25, 26]. One method to address this issue is the use of immersive, realistic, multisensory Virtual Reality (VR) environments, which may more accurately estimate a person’s cognitive, listening, or physical abilities during everyday behaviours e.g., [19, 27–29]. Moreover, while behavioural measures of hearing ability, like pure-tone audiometry, are useful for identifying the degree of hearing loss, self-reported hearing measures may be more ecologically valid. Indeed, self-reported hearing measures often consider functional difficulties, such as fatigue due to listening effort, across a variety of settings, which may more accurately reflect everyday listening difficulties [30]. Utilizing such techniques is therefore critical to enhance the ecological validity of hearing, cognitive, and mobility measures.

### Interventions for hearing loss

Hearing loss can begin in mid-life and has been reported to be the potentially largest modifiable risk factor for dementia [5, 6]. Hearing aids are a readily available rehabilitation strategy used to amplify the auditory signal at differing frequencies in order to restore the audibility of sound, with demonstrated benefits in terms of improved communication [31–33]. Evidence suggests that hearing aids may improve executive functioning [34] and speech-in-noise perception [35]. However, more randomized controlled trials are needed to corroborate the possible benefits of hearing aids on cognition. Similarly, the current evidence for the effect of hearing aids on mobility is mixed, with a need for more well-designed randomized controlled trials [36]. In addition to hearing aids, auditory training may be used as a rehabilitation strategy to improve speech perception through bottom-up (i.e., sensory refinement of sounds) or top-down (i.e., cognitive control) processes. A recent meta-analysis examining the pooled effect of auditory training on cognition in adults with hearing loss showed that auditory training led to transfer of learning to untrained cognitive tasks, particularly working memory and overall cognition [37]. However, none of the reviewed studies considered motor outcomes. As such, investigations into other interventions to prevent or mitigate cognitive and physical decline in older adults with hearing loss are warranted.

Improving higher level cognition through executive function training may be particularly beneficial as it directly targets the theoretical mechanisms of effortful listening. Accumulating evidence suggests that in normal-hearing older adults, executive function training can improve cognitive, motor, and dual-task performance [38–45]. While more limited, there is also some evidence to suggest that combined exercise and cognitive training may benefit cognitive and motor functioning in older adults with hearing loss [46, 47]. Li et al. [16] propose that cognitive interventions may increase compensatory scaffolding in response to declining motor and sensory systems with age via up-regulation of cortical activity in regions responsible for higher level cognitive functioning. However, the effect of executive function training on brain activity during dual-tasking in older adults with hearing loss has yet to be examined. Additionally, while some indicators of improved cognitive/mobility-related performance have been observed following lab-based training protocols, the broad application and generalizability of these training protocols is constrained. Instead, at-home cognitive training interventions would allow for more broadly accessible and scalable solutions for cognitive training. Indeed, the COVID-19 pandemic accelerated the development and use of tele-health applications increasing the feasibility of these approaches.

### Research objectives and hypotheses

Given the association between hearing loss and cognitive and physical impairment, there is great value in identifying treatment strategies targeted at delaying or mitigating further decline. The primary objective of our research is to establish the efficacy of an at-home computerized executive function training program on complex auditory and motor functioning measured under both laboratory and simulated real-world conditions. Behavioural and neuroimaging data will be collected in middle-aged and older adults with normal hearing sensitivity thresholds, as well as older hearing aid users.

It is hypothesized that executive function training will lead to greater improvements in dual-task performance compared to no training (i.e., wait-list control group). Furthermore, it is hypothesized that the greatest improvements will be seen in older hearing aid users, followed by older adults with normal hearing, and then middle-aged adults. We also predict a differential pattern of neural plasticity as a function of age/hearing group following executive function training.

## Methods/design

### Design

We will conduct a multi-site, single-blinded, randomized controlled trial involving at-home executive function training over a 12-week period. A total sample of 60 participants will be recruited at each testing site, comprised of 20 middle-aged adults (aged 45–60 years old) with normal hearing, 20 older-adults (aged 65–80 years old) with normal hearing, and 20 older-adults (aged 65–80 years old) with hearing impairment who use hearing aids (with a minimum of 6 months of experience using hearing aids). Participants will be randomized to either an executive function training group or a wait-list control group. The executive function training group will complete the home-based computerized cognitive training program during a 12-week period, while the wait-list control group will not complete any form of cognitive training during the 12 weeks. Participants in the wait-list control group will be offered the cognitive training program at the end of the study. Before and after the 12 week-period, participants in both groups will be asked to complete a series of cognitive, sensory, and mobility tests during two separate in-person sessions.

### Settings

Data collection will be conducted at two separate sites: Montreal (Concordia University), and Toronto (KITE-Toronto Rehabilitation Institute-University Health Network). Participants will be recruited through advertisements displayed at Concordia University’s PERFORM Centre and at the Toronto Rehabilitation Institute, advertisements displayed around the Montreal and Toronto communities (e.g., hospitals, community centres), print/online advertorials targeting our target populations (e.g., Senior Times Montreal), and by contacting participants who previously completed other studies in our labs.

### Participants

Participants will be asked if they were born biologically male or female and an equal number of males and females will be recruited into each group. Hearing loss is known to be more common, more severe, and has an earlier age of onset in males compared to females [48, 49]. A balanced design will therefore allow us to account for the known sex-related differences in hearing loss, in that we will be able to compare performance on our outcome measures across males and females.

### Inclusion criteria

To be enrolled in the study, participants must be aged 45–60 years old and have normal hearing, or 65–80 years old and have either normal hearing or bilateral hearing loss and use hearing aids (with a minimum of 6-months of experience using that set of hearing aids). Hearing ability will be assessed using pure-tone audiometry. An audiometric pure tone threshold average (PTA) will be calculated for each participant across 500 Hz, 1 kHz, 2 kHz, and 4 kHz. Participants will be included in the study if they have a PTA that is equal to or below 25 dB hearing level (HL) in the better ear for the normal-hearing middle-aged and older adults, and above 25 dB HL in both ears for the older adult hearing aid users [50]. While the grades of hearing loss have recently been updated [51], which categorize normal hearing as < 20 dB HL, we have opted to use the previous threshold of ≤ 25 dB HL for comparability with previous studies. All participants must be fluent English speakers and readers (i.e., monolingual or second language acquired early in life). Participants are also required to be physically present at Concordia University’s Loyola Campus in Notre-Dame-de-Grâce, Québec, Canada or the Toronto Rehabilitation Institute, University Centre in Toronto, Ontario, Canada, for a total of four in-person assessment sessions.

### Exclusion criteria

Participants will be excluded from the study if they have a learning disability, attention-deficit hyperactivity disorder, any major psychiatric illnesses (e.g., severe anxiety or depression), any previously diagnosed form of cognitive impairment, or any neurological, cardiovascular, orthopedic, or musculoskeletal conditions that may impede their mobility, concentration, or everyday functioning. Additionally, participants will be administered the Montreal Cognitive Assessment (MoCA) [52], a screening tool for mild cognitive impairment. A score of 26/30 or below on the MoCA may indicate possible mild cognitive impairment (MCI). However, more recent research has shown that a cut-off of 23/30 has better diagnostic accuracy and a lower false positive rate in detecting MCI [53]. As such, all participants must score above or equal to 23/30 on the MoCA, as well as perform within the age-normative range on all other neuropsychological tests (see details below). If a participant’s score on the MoCA falls below 23/30, or they demonstrate below average performance on any other neuropsychological test, they will be excluded from the study. Participants must not engage in any other cognitive training programs for the entire duration of the study and must maintain a consistent physical health lifestyle (i.e., not start a new intensive strength training regime midway through the study). Participants are also required to have normal or corrected-to-normal distance visual acuity and will be excluded if they score above 0.08 on the ETDRS Visual Acuity Chart [54], corresponding to a Snellen acuity equivalent of 20/24 or 6/7. This is an exclusion criterion as our study protocol has some visual requirements that participants need to be able to accomplish (e.g., neuropsychological testing, executive function training). Additionally, research has demonstrated that visual impairment, like hearing loss, is a potentially modifiable risk factor for dementia [55], so we want to control for this possible confound. Lastly, participants exhibiting poor mobility and balance on the Mini-BESTest [56], with a score falling below 16 out of 28, will not be included in the study due to an indication of potential motor difficulties [57].

### Sample size

Sample size calculation is based upon prior intervention studies that utilized the same cognitive training protocol and that reported pre- and post-training changes in our primary outcome measures (e.g., gait or postural variables, auditory working memory) for healthy older adults. Specifically, Pothier et al. [58] used the same executive function training as the current study combined with placebo stretching as one of four training groups and reported a significant Time (pre- vs. post-training) by Training Group interaction (total *n* = 90, *d* = 0.304, actual power = 0.96). For the group receiving the same cognitive training as the current study, a moderate effect of Time on gait speed was found (*n* = 23, *d* = 0.478), with an average increase of 0.13 m/s following training. Additionally, Bruce et al. [46] used a similar cognitive training protocol as the current study in combination with recumbent bicycling (delivered either sequentially or simultaneously), where a significant main effect of Training Group (sequential vs. simultaneous training format) was found for auditory *n*-back accuracy (*n* = 42, *d* = 0.718, actual power = 0.95). The effect size for auditory *n*-back improvement was large, whereas the effect size for gains in mobility was small to moderate. This is consistent with results from Downey et al. [40] where the same cognitive training protocol as the current study was utilized, demonstrating a large effect size for improvements in* n*-back dual-task costs (*g* = -0.83), but a small effect size for gains in walking speed dual-task costs (g =  − 0.11). The recommended (G*Power) sample size to achieve a power of 0.95 at an alpha level of 0.05 for the Training Group x Time interaction for walking speed is 18 per group. Therefore, we aim to recruit 20 participants in each of the three groups (normal-hearing middle-aged adult, normal-hearing older adults, older hearing aid users) to allow for 10% attrition and a balanced design.

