*Walking Task.* Participants will be required to walk on a treadmill at a self-selected speed at zero percent incline. Specifically, the speed of the treadmill will be gradually increased until the preferred speed is chosen and there are no signs of the participant sweating or being out of breath. The speed of the treadmill will be set at this speed for the duration of the experiment (i.e., will be the same speed across both single-task and dual-task conditions). During single-task conditions, participants must walk on the treadmill at their self-selected speed. During dual-task conditions, participants will simultaneously complete the 2-back task while walking. In order to measure the temporal characteristics of gait (i.e., mean and variability of step time, stride time), two electronic pressure sensors (TeleMyo Direct Transmission System) will be taped to the toe and heel of each shoe sole. Note that the treadmill will be running at the selected speed throughout the entire experiment in order to equate the same level of background noise (i.e., 50 dB SPL) across all trials.

There will be three different trial types (i.e., single-task walking, single-task 2-back, dual-task) and the experiment will follow an ABC-CBA sequence, which will occur two times, for a total of 12 trials. Dual-task costs (DTC; %) will be calculated for each of the walking and 2-back tasks: [(single-task – dual-task) / single task * 100]. DTC change scores will be calculated by subtracting the post-training DTCs from the pre-training DTCs.

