### StreetLab Protocol at UHN/KITE in Toronto

 Two dual-task paradigms will be conducted in StreetLab, a fully immersive, projection-based, VR simulator used to simulate realistic and challenging conditions (Fig. 1). StreetLab has a 240° horizontal by + 15° to -90° vertical field-of-view curved projection screen extending from the floor to ceiling. The virtual environment used in this study will depict a large urban 6-lane intersection street-crossing in Toronto. StreetLab is outfitted with an AMTI (Advanced Mechanical Technology, Inc., Watertown, MA) BP12001200–2000 strain gage force plate that measures ground reaction forces. There is a surround sound system with seven speakers (Meyersound MP-4XP; Meyersound Laboratories, Inc., Berkeley, CA) spatially distributed behind the projection screen, at approximately the height of a participant’s head when they are standing on the force plate positioned at 0**°** azimuth across a horizontal plane at ± 28° (right front and left front), ± 90° (right side and left side), and ± 127° (right rear and left rear). One subwoofer (Meyersound MP-10XP) is located in the floor under the centre speaker. All speakers are 2.14 m in depth from the participant when standing on the force plate (for more details of the acoustic properties of StreetLab, refer to [61]). Ambient traffic noise (e.g., vehicle traffic, bird noises) will be included to more closely simulate real-world acoustical conditions. The vehicle traffic will include moderate traffic density with approximately 10 cars appearing in the visual scene every 30 s. Participants will complete two dual-task paradigms that largely differ based on the two different cognitive auditory tasks to be performed, including 1) auditory 2-back task and 2) Coordinated Response Measures (CRM) task. The other primary difference from the Concordia site protocol is that instead of measuring walking as the primary mobility-related outcome measure, we will be measuring standing balance under different levels of cognitive and postural complexity.

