Linear mixed effects models will also be fitted for each of our outcome measures, particularly if there is a large amount of missing data or if there is an unequal amount of variance across groups. Specifically, Fixed effects will include Age/Hearing Group (middle-aged, older adult, hearing aid users), Training Group (executive function training, control), Sex (male/female), and Time (Pre- vs. Post-Training), Random effects will include the individual participants, and Covariates will include education.

Lastly, in order to elucidate whether brain activity reflects neural compensation or inefficiency, correlations between dual-task performance and HbO levels will be conducted at baseline and after 12 weeks. All statistical tests will be two-tailed, and a *p*-value of less than 0.05 will be considered to indicate statistical significance. Effect sizes will be calculated using Hedges’ *g.*

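### The only stated power (0.95 with 18 per group) is for walking speed, which is not a listed outcome, and 18 per arm does not give 0.95 for the quoted effects as labelled

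*Protocol article*

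**What the plan says.** The Sample size section of the protocol article makes one power statement for this trial. It begins "The recommended (G*Power) sample size to achieve a power of 0.95 at an alpha level of 0.05" and continues "for the Training Group x Time interaction for walking speed is 18 per group". The next sentence applies the number: "Therefore, we aim to recruit 20 participants in each of the three groups", these being the three age/hearing groups, with 10% allowed for attrition.

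The effect sizes quoted before it come from earlier studies:
- d = 0.304, a Time by Training Group interaction in a four-arm study (n = 90);
- d = 0.478, the Time effect on gait speed within one arm (n = 23);
- d = 0.718, auditory n-back accuracy, comparing two training formats;
- g = -0.83 for n-back dual-task cost, "but a small effect size for gains in walking speed dual-task costs" (g = -0.11).

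On what is measured, the Walking Task at Concordia says "The speed of the treadmill will be set at this speed for the duration of the experiment", and adds that single- and dual-task conditions share that speed. The gait variables are introduced with "In order to measure the temporal characteristics of gait (i.e., mean and variability of step time, stride time". In the StreetLab section, KITE differs from Concordia in that "instead of measuring walking as the primary mobility-related outcome measure, we will be measuring standing balance". The primary outcomes in Primary outcome measures and Planned analyses are cognitive accuracy and reaction times, temporal gait variables, posturography and dual-task costs. Speed is in neither list.

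**The concern.** A power statement tells the reader what a null result on a named outcome would mean. Here the named outcome is not one the trial says it will analyse, and the belt holds it constant across the conditions that define the dual-task comparison. A reader could take 0.95 as applying to step time, stride time or posture and read a null result there as strong evidence of no benefit. The same section describes the mobility gains in one of the earlier studies as small to moderate.

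The number is also hard to connect to its inputs. A Training Group x Time calculation counts people per training arm, yet 18 is applied to age/hearing groups, each of which is then divided between the arms. None of the quoted walking effects looks large enough, as labelled, to give 0.95 power with 18 per arm.

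**Working it through.** **Inputs from the article.** Power 0.95 and alpha 0.05 (Sample size); "All statistical tests will be two-tailed" (Planned analyses); 60 per site (Design); equal allocation within each age/hearing group (Randomization); 10% attrition (Sample size).

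**Assumptions.** The article does not give the pre-post correlation r, so a range is used. Control change is set to zero where only a within-arm effect is quoted. Covariates are ignored.

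**1. Attrition.** 18 / 0.9 = 20. This step reproduces.

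**2. Meaning of group.** 20 per age/hearing group splits 10 v 10, or 9 v 9 after 10% loss. The planned overall interaction at one site has 60 x 0.9 = 54 completers, or 27 v 27. Neither is 18 v 18.

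**3. Trying to reproduce 18.** For G*Power's within-between interaction with m = 2 time points, lambda = N f² m / (1 - r). With two arms and r = 0.5:
- f = 0.304, N = 36 (18 per arm): lambda = 36 x 0.0924 x 2 / 0.5 = 13.31, power 0.943. N = 38 gives 0.954.
- f = 0.478, N = 18 in total: lambda = 18 x 0.2285 x 2 / 0.5 = 16.45, power 0.967. N = 16 gives 0.944.

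So figures at or near 18 appear when a value the article labels d is entered as f.

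**4. What that entry means.** In a 2 x 2 interaction each cell departs from additivity by one quarter of the between-arm difference in change, so f = d/4. Then f = 0.304 corresponds to d = 4 x 0.304 = 1.216. A two-sample t test on change scores with d = 1.216 and 18 per arm also gives 0.943, which confirms the conversion.

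**5. Taking the values as d.** The test is a two-sample t on change scores (noncentral t), with d_change = d / sqrt(2(1 - r)). With 18 per arm, 0.95 power needs d_change = 1.24. At r = 0.5, d = 0.304 would need 283 per arm and d = 0.478 would need 115.

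| Quoted effect | Per arm | r = 0.5 | r = 0.7 | r = 0.8 |
|---|---|---|---|---|
| 0.478 | 18 | 0.29 | 0.44 | 0.60 |
| 0.478 | 27 | 0.41 | 0.60 | 0.78 |
| 0.11 | 27 | 0.07 | 0.08 | 0.10 |
| 0.83 | 27 | 0.85 | 0.97 | 0.997 |

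For d = 0.478 with 18 per arm, r would have to be about 0.93 to reach 0.95. The 0.478 is a within-arm change with no control change subtracted, so these powers are, if anything, generous unless controls get worse.

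**6. Detectable differences per site, 27 v 27.** 0.78 SD of change at 0.80 power and 1.00 SD at 0.95 power.

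**The case against.** The strongest reply is that 18 can be reached from the quoted effects. That is true: step 3 shows two routes, and a reader who infers that 18 has no source in the section goes too far. Both routes use Cohen's f, however, while the article labels the values d. The article does not show whether the label or the entry is wrong. A milder conversion, f = d/2, would bring 0.478 to 0.95 with 18 per arm at r of about 0.70, but that conversion belongs to a two-group main effect and doubles the difference implied for an interaction.

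A reader might also infer that every primary outcome falls below 0.95. The article does not support that. If 0.83 for n-back dual-task cost is a training-versus-control difference, 27 v 27 gives 0.85 at r = 0.5 and 0.97 at r = 0.7. Absence of stated power is not proof of low power. Nor can the 0.85 be adopted as it stands, because the article does not say that g = -0.83 is such a contrast.

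Two further limits stand. The fixed belt rules out a dual-task cost in speed but not a pre-post change if speed were chosen again after training; the article neither says that this happens nor lists speed as an outcome. And 9 v 9 within an age/hearing group is not the planned primary test, which has 27 v 27 per site. The planned age/hearing comparison is a one-way ANOVA within the training arm.

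An article may leave the entered effect and correlation to a fuller document. That does not answer the point that the statement it does make concerns an unlisted outcome and uses group in two senses.

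**Conclusion.** The point holds in this form. The stated 0.95 power applies to no outcome the trial lists; this follows from the text alone and needs no assumption. The change in the meaning of group also follows from the text.

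The numerical part is conditional. With the quoted effects taken as d and retest correlations of 0.5 to 0.8, 18 per arm gives 0.29 to 0.60 for the gait-speed effect, not 0.95. At the planned 27 v 27 the same effect gives 0.41 to 0.78, and the quoted dual-task walking effect gives 0.07 to 0.10. Pooling the sites would not help gait or posture, since each is measured at one site only. No primary outcome is shown to have 0.95 power; the cognitive outcomes may have it under favourable assumptions.

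**What to change.** - Delete the walking-speed power claim.
- Restate the section for the planned size, about 27 v 27 completers per site, and for an outcome the trial measures. Give the effect-size metric, the assumed between-arm difference in change, the retest correlation as a range, and what group means.
- State the detectable difference per site: 0.78 SD of change at 0.80 power and 1.00 SD at 0.95.
- Say that 0.95 power is not claimed for gait or posture at the small-to-moderate effects quoted, nor for the age/hearing comparisons.
- If the 2-back task is chosen, report power as a range (for 0.83: 0.85 at r = 0.5, 0.97 at r = 0.7) and state as an assumption that 0.83 is a training-versus-control difference.

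The cost is rewording. Recruitment, conduct and analysis are unchanged. The downside is a less favourable power statement.
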